We have demonstrated that approximately 50% of patients with untreated OUD in the ED are not eligible for initiation (induction) of buprenorphine at the time of their ED visit due to insufficient severity of opioid withdrawal. In order not to miss this important and substantial patient population, it is imperative to investigate strategies for ED-based initiation of BUP. Our work, and others, demonstrates the safety and efficacy of unobserved (e.g., home) BUP induction in patients, including those in the ED, with low withdrawal severity. As the pharmacology of XR-BUP, in contrast to SL-BUP, has a slower onset of activity at the mu opioid receptor, it lends itself to direct induction in individuals with low COWS scores (COWS < 8) from the ED. The median time to peak concentration is 24 hours versus about 2.5 hours for SL-BUP. However, serum concentrations of buprenorphine with XR-BUP are rapidly detectable which likely results in adequate BUP to provide adequate relief of withdrawal. Thus, we will conduct a small ancillary study of approximately 75 patients in approximately 4-10 sites with ED clinicians who have experience with BUP inductions. This ancillary study will inform the larger pragmatic trial and potentially expand recruitment in the Effectiveness RCT component to include ED patients with COWS <8. The goal will be to allow expansion of the Effectiveness RCT to ED patients with COWS <8 allowing for randomization in this group of patients to ED initiated XR-BUP vs.

unobserved induction with a prescription for SL-BUP (See Potential modifications to Effectiveness RCT based on Ancillary Study Component below).

It is advantageous to develop electronic health record (EHR) phenotypes of opioid-related illnesses that accurately and automatically characterize ED visits, enhance active disease surveillance, and better identify patients potentially eligible for study inclusion, increasing the generalizability of trial findings. Thus, we include an EHR phenotype development and validation aim that will aid the proposed current and future opioid-related research trials in EDs.

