#### 8.4.9 Interventions: Buprenorphine Induction and Discharge Instructions

Uniform BUP induction protocols will be used:

a) Standard SL-BUP:

- i. COWS  $\geq 8$ : Patients will receive 4mg of SL-BUP for a COWS score of 8-12 (mild withdrawal). After 30-45 minutes if tolerated and no unanticipated adverse reactions, an additional 4mg can be administered for a total of 8mg in the ED. Patients presenting with moderate-severe withdrawal ( $\text{COWS} \geq 13$ ) will receive an initial dose of 8mg SL-BUP. All patients will receive a buprenorphine prescription and instructions for additional BUP doses to allow for up to a dose of 12mg if needed, and for 16mg each subsequent day until their scheduled follow up appointment for ongoing MOUD.
- ii. COWS 4-7: Patients will be provided with a uniform set of instructions to guide unobserved (home) induction. They will be prescribed doses of SL-BUP to allow them to take dose up to 12mg in the 24 hours after discharge. All patients will also receive a buprenorphine prescription for 16mg each subsequent day until their scheduled follow up appointment for ongoing MOUD.

b) XR-BUP Injection with CAM2038 24 mg: Based on published data for equivalency of 16mg of SL-BUP and experience with the phase 3 trial, patients will receive a 24mg dose of injectable CAM2038 in the ED on Day 0. The patient will remain in the ED for 2-hours post injection to observe for worsening withdrawal or precipitated withdrawal as defined below in Section 9.8.

- i. SL-BUP Rescue Dose: If patient's COWS score is  $> 12$  after XR-BUP injection, a 4-8 mg dose of SL-BUP can be administered.

Patients can receive any of the ancillary medications per standard of care for specific symptoms of withdrawal. Example includes ondansetron for nausea or acetaminophen for headache.

Discharge Instruction: Participants randomized to XR-BUP will receive a wallet card with instructions for signs and symptoms of precipitated withdrawal and advice to return to the ED for immediate evaluation for the first 24 hours post dosing if precipitated withdrawal is suspected. Each ED will have a clinician on call for the study to assist in assessment and treatment.

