#### 8.4.11 Precipitated Withdrawal with XR-BUP

Clinicians will assess patients whose COWS increases to > 12 within 1 hour of administration and determine if the event is considered a precipitated withdrawal. This clinical determination will be based on the severity of the withdrawal signs and symptoms, the rapidity of the onset of withdrawal symptoms, and clinical factors (e.g., timing since last use of an opioid agonist(s), type(s) of opioid agonist, duration of action of opioid agonist(s) used, and route of administration). Scores will be based on objective components, eliminating nausea which can be a side effect of the BUP administration.

Patients who experience precipitated withdrawal will be treated with ancillary medications as described above. We will collect information that may predispose participants to precipitated withdrawal on all participants. This will include recent exposure to buprenorphine, fentanyl, and other opioids via urine testing and self-report, and receipt of naloxone in the ED or pre-hospital setting. This information will be collected on the Precipitated Withdrawal form (PWD), Urine Drug Screen (UDS) form and the Timeline Followback Supplement (TFS) form, which is a supplement to the Timeline Followback that solicits substance use for 24 hours prior to enrollment.

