### 9.1 Study Procedures and Assessments

#### 9.1.1 Rationale for Study Component

Induction with SL-BUP is typically restricted to patients with mild to moderate opioid withdrawal syndrome as manifested by a COWS score  $\geq 8$  to avoid precipitated withdrawal. Precipitated withdrawal occurs when a partial agonist such as buprenorphine displaces a full agonist such as heroin. Given the unique pharmacology of CAM2038, which results in a slower onset of action at the mu opioid receptor, it is potentially feasible to consider induction in patients with COWS < 8. In fact, in a recently published trial by Drs. [name] and [name], a small number of individuals were provided CAM2038 with COWS < 8 without incident. If these findings are replicated in the current ED-based study, this will allow for expanded eligibility criteria in the Effectiveness RCT component of this research, and the potential to serve a larger patient population.

#### 9.1.2 Overview of ED XR-BUP for COWS < 8

We will conduct a case series,  $n=75$ , of induction of XR-BUP in patients with COWS scores < 8. This will be performed in approximately 4-10 EDs by Emergency Medicine physicians who have experience with BUP induction procedures. We will be testing the administration of XR-BUP in patients who present with a COWS < 8 and assess withdrawal signs and symptoms every 30 minutes for 4 hours. Following ED discharge, data will be collected daily regarding withdrawal signs and symptoms and patient satisfaction through day 7.

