### 9.5.5 Daily Follow-up Assessments (Days 1-6)

Follow-up assessments will be conducted once daily via text/phone by the RAs. Assessment of desire to use, and opioid and other drug use will be collected. To improve data completeness, in advance of scheduled study assessments, the RA will remind the participant via telephone call, text, email and/or social media (based on study participant preference) prior to the scheduled time for each follow-up assessment.

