### 9.8 Precipitated Withdrawal

Clinicians will assess patients whose COWS increases to > 12 during the 4 hours of observation post administration and determine if the event is considered a precipitated withdrawal. This clinical determination will be based on the severity of the withdrawal signs and symptoms, the rapidity of the onset of withdrawal symptoms, and clinical factors (e.g., timing since last use of an opioid agonist(s), type(s) of opioid agonist, duration of action of opioid agonist(s) used, and route of administration). Scores will be based on objective components, eliminating nausea which can be a side effect of the BUP administration.

Patients who experience precipitated withdrawal will be treated with ancillary medications as described above.

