#### **3.2.2.5 Treatment Emergence**

Treatment emergence is used to determine the temporal relationship of an adverse event to study treatment administration. The window for treatment emergence begins on the day of first dose and ends 30 days later (first dose date to first dose date + 30 days, inclusive). The first dose date for XR-BUP will be the date the injection was administered in the ED. The first dose date for SL-BUP will be the date of enrollment provided the medication was administered in the ED or prescribed for home induction.

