#### **8.2.4 Precipitated Withdrawals**

A table summarizing the number of participants experiencing a precipitated withdrawal as well as the number of such withdrawals will be generated by treatment arm. A listing of precipitated withdrawals will be provided.

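### The RCT table of precipitated withdrawal by arm rests on unequal ascertainment: its only scheduled assessment is in the ED, while SL-BUP participants with COWS 4-7 start treatment at home

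*Combined protocol and SAP*

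**What the plan says.** SAP 8.2.4 plans a count of participants with precipitated withdrawal, and the "number of such withdrawals will be generated by treatment arm". It names no source form, time window, percentage or denominator. SAP 8.2 and the table list in SAP 16.2 place the table in the safety population, which SAP 3.2.1.3 defines as consented participants who received treatment, analysed by randomized arm.

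On SL-BUP induction at COWS 4-7, protocol 8.4.9 says: "Patients will be provided with a uniform set of instructions to guide unobserved (home) induction". SAP 3.2.2.5 dates their first dose at enrolment, "provided the medication was administered in the ED or prescribed for home induction", and SAP 6.2.1 counts them as exposed if sent home with an induction dose. XR-BUP participants stay in the ED for 2 hours after injection (8.4.9).

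Protocol Table 2 schedules the PWD form once, in the enrolment column. No precipitated-withdrawal item appears at Day 7 or Day 30.

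The windows differ. Section 8.4.11, headed for XR-BUP only, says: "Clinicians will assess patients whose COWS increases to > 12 within 1 hour of administration". Section 8.4.9 instead refers to 9.8 for the definition, and 9.8 says: "Clinicians will assess patients whose COWS increases to > 12 during the 4 hours of observation post administration". There is no matching rule for SL-BUP.

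**The concern.** Precipitated withdrawal is the harm most closely tied to starting buprenorphine, and a by-arm table invites the reader to compare the two inductions on it. That comparison needs a similar chance of recording an event in each arm. Here every injected participant is watched for 2 hours, while part of the SL-BUP arm takes the first dose where nobody is observing and has no later scheduled question about withdrawal. Those participants still count as treated.

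The XR-BUP arm has a gap of its own. Protocol 3.1 says: "The median time to peak concentration is 24 hours versus about 2.5 hours for SL-BUP". The discharge wallet card in 8.4.9 tells XR-BUP participants to return within 24 hours if they suspect precipitated withdrawal, so the protocol itself allows for events after discharge. No scheduled form looks for them.

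At stake is whether the trial can say which induction causes less precipitated withdrawal, above all at COWS 4-7, where place of first dose and treatment arm coincide.

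**Working it through.** The documents give no expected rate of precipitated withdrawal by arm in the RCT, so there is no stated figure to reproduce. The check sets the provisions side by side and then illustrates the possible size.

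**Step 1. Opportunity to record an event**

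| | XR-BUP, all COWS | SL-BUP, COWS >=8 | SL-BUP, COWS 4-7 |
|---|---|---|---|
| First dose (8.4.9) | ED | ED | Home, unobserved |
| Stated ED observation after first dose | 2 hours | No fixed period; an interval of 30-45 minutes before a second dose at COWS 8-12 | None |
| Assessment rule | 8.4.11 (1 hour) or 9.8 (4 hours) | None stated | None stated |
| PWD form (Table 2) | Index visit | Index visit | Index visit, before the first dose is taken |
| Scheduled item after discharge | None | None | None |
| In safety population | Yes | Yes | Yes |

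The COWS >=8 column is the induction protocol. SAP 3.2.1.2 foresees that some of these participants will opt for home induction.

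**Step 2. Other routes to a record**

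- Protocol 8.9.4 excepts precipitated withdrawal from the events that need not be reported as AEs, with reporting to day 30. Section 14.24.1 lists withdrawal without that exception.
- Section 8.9.4 starts the reporting period at XR-BUP administration; 14.24.1 starts it at administration of study product. Table 2 has a row for serious adverse events (death) but none for AEs in general.
- The ED Visits and Hospitalizations form (8.7.20) captures return visits to Day 30 by patient report and EHR. SAP 8.2.8 tabulates ED visits without asking for precipitated withdrawal as a reason.

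Some later events can therefore be recorded, but passively and under conflicting rules, and SAP 8.2.4 does not say that they enter its table.

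**Step 3. Illustration for SL-BUP**

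Let p be the true rate, assumed equal for ED and home inductions, h the home-induced share, and c the share of home events that reach the table. Then

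tabulated rate = p × [(1 − h) + h × c].

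The documents give neither h nor c. I assume h from 10% to 50%.

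| h | c = 0 (PWD form only) | c = 0.5 | c = 1 |
|---|---|---|---|
| 10% | 0.90p | 0.95p | p |
| 25% | 0.75p | 0.875p | p |
| 50% | 0.50p | 0.75p | p |

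With about 1000 per arm (2000 ÷ 2) and an assumed p of 3%, the true count is 30. At c = 0 the table shows 27, 22.5 or 15.

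**Step 4. Illustration for the comparison**

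Let l be the share of XR-BUP events that occur after the ED stay and go unrecorded. With equal true rates and c = 0,

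tabulated ratio XR/SL = (1 − l) ÷ (1 − h).

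- l = 50%, h = 10%: 0.50 ÷ 0.90 = 0.56
- l = 25%, h = 25%: 0.75 ÷ 0.75 = 1.00
- l = 10%, h = 50%: 0.90 ÷ 0.50 = 1.80

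A true ratio of 1 can appear on either side of 1.

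**Step 5. The ancillary study**

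Protocol 9.1.2 says: "Following ED discharge, data will be collected daily regarding withdrawal signs and symptoms and patient satisfaction through day 7". For Days 1-6, section 9.5.5 says: "Assessment of desire to use, and opioid and other drug use will be collected". Table 3 likewise lists only substance use and desire to use on those days. The sections do not agree.

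**The case against.** A reader might infer that precipitated withdrawal is recorded only in the ED, that home-induced participants can never have an event, and that the table therefore understates SL-BUP and is biased against XR-BUP. The documents do not support that. Section 8.9.4 makes precipitated withdrawal a reportable AE to day 30, return ED visits are captured, and SAP 3.2.2.5 gives home-induced participants a 30-day treatment-emergent window. SAP 8.2.4 names no source, so understatement depends on the PWD form being the only one. Step 4 shows why the net direction cannot be stated.

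It is also tempting to say that late XR-BUP events are missed. Under the 1-hour rule in 8.4.11, with speed of onset as a criterion, a late event would not be assessed as precipitated withdrawal at all. Under 9.8 or the wallet card it might be. This depends on a definition the sponsor has not settled. A 1-hour rule within a 2-hour stay is not itself contradictory; the conflict is the pointer to 9.8.

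The 50% end of the range for h is loose. Protocol 3.1 says that about half of untreated ED patients lacked sufficient withdrawal in earlier work. That is not the COWS 4-7 share of this trial, which excludes COWS 0-3 and required COWS >=8 before the expansion.

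The table is descriptive, and precipitated withdrawal is neither an RCT hypothesis nor a listed secondary outcome. The ancillary criteria for expanding eligibility were 1-hour and 4-hour outcomes, so the Days 1-6 mismatch does not undermine them.

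These objections limit the claim about size and direction. They leave standing that the one scheduled form gives the arms unequal chances of detection.

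**Conclusion.** The point holds as a matter of ascertainment. The only scheduled assessment of precipitated withdrawal is at the index ED visit. SL-BUP participants with COWS 4-7 cannot be observed on it after a first dose, yet they belong to the population tabulated. Neither arm is assessed on schedule after discharge, and the passive routes run under rules that conflict. SAP 8.2.4 does not settle source, window or denominator.

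If the PWD form alone is used, the SL-BUP rate is understated by the home-induced share: 10% to 50% in relative terms over the assumed range, and less to the extent that home events arrive by other routes. The between-arm ratio could run from 0.56 to 1.80 at a true ratio of 1. These figures rest on assumed h and l, on equal true rates, and on no capture of home events. They show that the error can go either way and do not estimate it.

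**What to change.** **In SAP 8.2.4.** Name the source forms and the denominator, and count events in one common post-dose window in both arms. Tabulate by randomized arm within baseline COWS strata, 4-7 and >=8. Treat COWS >=8 as the main in-ED comparison, and state how many in that stratum opted for home induction. In COWS 4-7, flag home-induced SL-BUP participants as not observed and present no between-arm contrast from the ED form. Report post-discharge events (AE reports, return ED visits) separately by arm.

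Do not restrict the table to ED-dosed participants across all COWS scores. That would remove COWS 4-7 from SL-BUP but keep it in XR-BUP, and so break the randomized comparison.

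**In data collection, if enrolment is still open.** Add one withdrawal item to the existing Day-7 call in both arms. The answers are self-reported and cannot be adjudicated by COWS, so they belong in the separate post-discharge display.

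**For the sponsor to reconcile.** Sections 8.4.9, 8.4.11 and 9.8 on the window; 8.9.4 and 14.24.1 on AE reporting and its start; and, for the ancillary study, 9.1.2 with 9.5.5 and Table 3 on daily withdrawal data.

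**Cost.** SAP wording, which fits the revision history's plan to finalize the RCT sections in version 4.0 before database lock, plus about one minute on a scheduled call if the item is added. The price is that COWS 4-7 yields no in-ED contrast between arms.

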#### **8.2.5 Additional Medications**

Additional medications are collected on the WWM eCRF and will be summarized by treatment arm. The table will include the number of participants who received no additional medication after the initial protocol medication, the number who received any additional medications, and the number receiving each type of additional medication. For medications that can be taken via more than one route, the number of participants receiving the medication via each of the routes will be summarized. Summary statistics (mean, median, mode) will be provided for the total dose administered (in milligrams) for each medication.

A listing of participants who received additional medications and the medications received including route and dose will be provided.

#### **8.2.6 Deaths**

A listing of deaths will be presented and will include all variables in the AE listing described in Section 8.2.1.

#### **8.2.7 Overdoses**

Overdoses are a secondary efficacy endpoint. Details on the outcome and method of analysis are described in Sections 7.2.4.7 and 7.2.5.7.

#### **8.2.8 Hospitalizations and ED Visits**

A table summarizing hospitalizations post index ED visit will be provided by treatment arm. The table will include the number of hospitalizations, the number of participants with a hospitalization, the distribution of hospitalizations per participant, and the number of days of hospitalization per participant.

A similar table summarizing ED visits after the index ED visit will be provided. Separate listings of hospitalizations and ED visits will be generated.

### **9.0 SIGNIFICANCE TESTING AND MULTIPLICITY**

#### **9.1 Ancillary Component**

No hypothesis testing is performed on the primary outcome measures and no adjustment for multiple hypothesis testing is immediately relevant.

#### **9.2 RCT Component**

All p-values will be assessed at the 0.05 level. There is a single primary outcome, and there are no plans to adjust supportive or secondary analyses for multiplicity.

### **10.0 SAMPLE SIZE AND POWER**

#### **10.1 Ancillary Component**

The sample size of 75 in the ancillary component is justified on the basis of acceptable 95% confidence interval (CI) widths, where the confidence intervals are determined using the Exact

Clopper Pearson method. The table below summarizes the widths of such confidence intervals for various estimated proportions.

| Proportion      | 0.01  | 0.05  | 0.1   | 0.15  | 0.2   | 0.25  | 0.3   |
|-----------------|-------|-------|-------|-------|-------|-------|-------|
| Actual CI Width | 0.066 | 0.113 | 0.148 | 0.173 | 0.192 | 0.206 | 0.217 |

If the proportion is 0.01 (or 1%) the 95% confidence interval will have a width (i.e., difference between upper and lower 95% confidence bounds) of 0.066 (or ~7%). Point estimates of 5%, 10%, and 20% will have widths of 11%, 15% and 19% respectively.

Based on results presented to the DSMB in April 2021 on the initial 75 patients, desire to capture more information on patients with a COWS score of 0-3, and DSMB recommendation in May 2021, recruitment for the ancillary component will continue until a sample size of approximately 100 is achieved. The additional 25 patients to be enrolled will be exclusively in the COWS < 4 group.

## 10.2 RCT Component

A sample size of 850 per group/treatment arm was required to ensure 90% power at the two-sided 0.05 significance level to detect a difference in the proportion engaged in formal addiction treatment at Day 7 of 8 percentage points between SL-BUP and XR-BUP, assuming 45% engaged for SL-BUP and 53% engaged for XR-BUP. This is calculated based on a simple two-sample proportion test. This sample size also provides greater than 80% power to detect improvements of 7% (as opposed to 8%). Given the conservative nature of a 45% estimate in the control group (SL-BUP) used, any actual rate in the control group would allow at least 80% power to detect a treatment effect of 7% and at least 90% power to detect a treatment effect of 8%. A sample size of approximately 2,000 was then chosen to accommodate a roughly 15% dropout rate. Power estimates for differing rates in the SL-BUP group and treatment effects are provided in Figure 1.

**Exhibit 3: Power (N = 850 per group) for Variations of Difference in Treatment Engagements Between SL-BUP and XR-BUP**

[figure not shown]

For secondary outcomes such as self-reported days of illicit opioid use, craving, and satisfaction scores, this sample size will provide 90% power to detect relatively small standardized differences (Cohen's  $d = 0.16$ ) between the two intervention groups. Figure 2 below shows detectable risk

ratios for different proportions of participants with an overdose event within 30 days in the SL-BUP treatment arm, which is not expected to be high. If the proportion is 15%, there will be sufficient power to detect a risk ratio of 0.70 and if it is 2%, there will be sufficient power to detect a risk ratio of 0.25.

**Exhibit 4: Detectable Risk Ratios for Overdose Outcome as a Function of Proportion of Participants with Overdose Events in the SL Group (80% Power)**

[figure not shown]

